### Objectives

The objectives of this study are to 1) examine the effectiveness of event notification on health outcomes for older adults who experience acute care events, and 2) compare approaches to responding to event notification.

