### Trial design

We will implement a multi-year, mixed methods study involving a clinical trial of the HIE intervention and qualitative examination of its implementation. A 2-site cluster-randomized trial will examine the impact of event notification introduced into multiple primary care medical homes part of a large integrated health system.

The trial involves three arms recruited in two phases as depicted in Fig. 1. In Phase 1, we will identify and enroll active subjects into one of two groups: 1) event notification only, in which the primary care provider is alerted when the subject has an acute care event outside the integrated health system; or 2) event notification plus geriatric care transitions intervention, in which the primary care provider is alerted in parallel with a geriatric care coordinator who will facilitate a standardized care transitions intervention for 30 days following discharge from the acute care facility. Assignment is based on the patient’s primary care medical home, which will be randomized to one of the arms. In Phase 2, we will retrospectively identify and capture data on a third group of concurrent control patients for which no notification or post-acute care transitions intervention was utilized. Comparisons will be performed between each intervention group and the control group as well as between the two intervention groups.

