### Sample size

Our sample size estimate is based on the primary outcome. Reports of randomized studies of geriatric care transitions interventions have reported 25–45% reductions in hospital readmissions [17, 20, 29]. Based on prior work as well as pilot data gathered within the VHA (unpublished), we postulate that the notification-only group as well as the usual care group will have a 40% readmission rate while the notification-plus-coordination group will have a 26% readmission rate in the 90-day post-discharge period (i.e., a clinically significant 35% reduction).

There are several features of the study that support this large potential effect. First, the targeted patients are at high risk of readmission because they are older veterans who utilize both VHA and non-VHA services, who have been shown in previous studies to have significantly higher readmission rates after acute illness. Second, in contrast to veterans hospitalized in the VHA who routinely receive PACT post-discharge telephone calls and follow-up, this group is naïve to any coordination intervention because PACT teams normally do not respond to non-VHA hospital encounters because they do not know about them. Thus, we postulate more than an incremental effect.

To account for possible dependence of the outcome among patients cared for by the same PACTs (clustering), we estimated the design effect [30] based on an average number of subjects per PACT = 7. Assuming the intraclass correlation is 0.05 (based on pilot data and prior literature [31]), we need to observe a total of 466 patients with non-VHA hospitalizations or ED visits (155 in the notification-plus-coordination group and 311 combined in the notification-only and usual care groups) to detect an effect size of 0.35 with 80% power and a two-tailed test at 5% significance. If the intraclass correlation is smaller (e.g., 0.04), which may be the case for a group of patients whose care is fragmented and perhaps less influenced by primary care team clustering, then the power will be higher.

In order to achieve the target sample size, we will enroll 300 patients at each site, with an estimated 25–30% of enrolled veterans experiencing non-VHA hospital encounters. We anticipate 10–15% attrition due to death or loss to follow up given the average age of veterans in the target population.

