### Allocation

We will cluster randomize by PACT team to prevent a team from having patients in both treatment groups and reduce contamination. Prior to initiating enrollment, the lead investigator ([name]) will assign PACTs to notification-plus-coordination or notification-only groups, using lists of computer-generated random numbers in a 1:1 ratio, with separate lists for the Bronx VA and Indianapolis VA, in order to maintain balance in groups within each study site. There are 25 primary care PACTs in the Bronx and 41 in Indianapolis, and each PACT will keep its group assignment for the duration of the study. In Phase 1, enrolled patients will be assigned to notification-plus-coordination or notification-only groups according to their assigned PACT team.

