### Statistical methods

All analyses will be performed as intention-to-treat (ITT), i.e. all outcomes will be included on patients assigned to treatment groups, even if they deviate from the group’s intervention. We will use a generalized linear mixed (GLM) model to test the effect on the primary outcome of 90-day hospital admission or readmission (e.g., 0 = no, 1 = yes). The logit link of the binary outcome for each observation will be modeled as a linear model, with the PACT team used as a random effect and group assignment (e.g., 0 = notification only or no notification, 1 = notification-plus-coordination) as a fixed effect. Inclusion of random effects in the model accounts for possible within-cluster correlation of the outcome since patients will be clustered by PACT.

To estimate the intervention effect after accounting for patient characteristics, especially those found to be imbalanced between study arms from the preliminary analyses, other covariates will be added as fixed effects to the model. These covariates may include: age, gender, non-VHA hospital, number of pre-admission medications, chronic illness count, discharge diagnosis, and length of stay for the index admission (with ED visits coded as 0 days). In addition to bias reduction, this analysis may increase the power for detecting the intervention effect by reducing the unexplained variance of the outcome and add insight into factors that predispose these patients to the outcome.

A similar approach will be used to test the intervention effect on secondary outcomes. For each secondary outcome, an appropriate distribution or link function will be chosen for the GLM model, e.g. logit link for the binary outcome of scheduled follow-up, Poisson or Negative Binomial distribution for the counts of high-risk medication discrepancies, identity or other links for Care Transitions Measure depending on the distribution of scores.

All analyses will be carried out using the most recent version of SAS (Carey, North Carolina, USA) available to VHA researchers using the VHA computing environment. For all tests, we will use 2-sided *p*-values with alpha = < 0.05 level of significance. Qualitative coding and analysis will be conducted using the most recent version of NVivo (QSR International; Doncaster, Victoria, Australia).

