Furthermore, although we considered using a third, “usual care” arm for enrolled patients like most trials instead of the second phase, we ultimately deemed it potentially unethical to deny patients a potentially valuable event notification intervention. Ethical dilemmas with respect to randomization are common in biomedical informatics intervention studies [48], which often require quasi-experimental approaches [49]. Moreover, the number of primary care medical homes distributed across the two sites would limit statistical power if they were divided into thirds for randomization. Therefore we opted to retrospectively use patients who did not enroll in the study or who enrolled but had a non-system encounter outside the prospective monitoring period as a control arm. Doing so enables us to retain the robustness of randomization in arms 1 and 2 while maintaining statistical power with arm 3.

Another challenge for the study will be the implications of the findings. Should the care transitions intervention in combination with event notification prove to be superior, how can the VHA feasibly disseminate this approach? Furthermore, how can health systems economically sustain such an approach? The care transitions intervention requires active monitoring by a social worker or other care coordinator following discharge from the “out-of-network” facility. A home visit and phone monitoring may not be possible in every care transition. A challenge for our team will be to determine under what circumstances a superior but more intense intervention would be cost effective for the VHA or another health system.

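### The primary model's single 0/1 group term pools the randomised notification-only arm with non-randomised usual-care patients, so its coefficient is only partly a randomised contrast and cannot isolate the effect of notification

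*Protocol article*

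**What the plan says.** **What is randomised.** The Allocation section says that the lead investigator "will assign PACTs to notification-plus-coordination or notification-only groups, using lists of computer-generated random numbers in a 1:1 ratio", with separate lists by site. No team is randomised to usual care.

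**Where usual care comes from.** The Trial design section states that in Phase 2 "we will retrospectively identify and capture data on a third group of concurrent control patients". The Discussion explains that the plan is to "retrospectively use patients who did not enroll in the study or who enrolled but had a non-system encounter outside the prospective monitoring period" as the control arm.

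**What is compared.** Objective 1 is to "examine the effectiveness of event notification on health outcomes for older adults who experience acute care events". The Trial design section adds: "Comparisons will be performed between each intervention group and the control group as well as between the two intervention groups".

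**What is modelled.** The Statistical methods section gives one model for the primary outcome: a logistic mixed model with PACT as random effect and "group assignment (e.g., 0 = notification only or no notification, 1 = notification-plus-coordination) as a fixed effect". Covariates may be added as fixed effects.

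**What is powered.** In the Sample size section, "we postulate that the notification-only group as well as the usual care group will have a 40% readmission rate", against 26% with coordination. The requirement is 155 patients in the coordination arm and 311 in the other two groups combined.

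**What is claimed.** The Discussion says of the retrospective arm: "Doing so enables us to retain the robustness of randomization in arms 1 and 2 while maintaining statistical power with arm 3". It also says the study is sized to examine both the benefit of notification and the added benefit of care transitions support.

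**The concern.** Code 0 holds two kinds of patient. Notification-only patients are there by randomisation of their team. Usual-care patients are there because they did not enrol, or because their encounter fell outside the monitoring period. The coefficient for code 1 against code 0 is thus partly a randomised comparison and partly an observational one, and the two parts cannot be told apart in the result.

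Three things follow.

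1. Differences in risk or ascertainment between enrolled and non-enrolled patients can enter the primary effect. Enrolment requires consent to health information exchange, and the exchange networks are one source of outcome data, so ascertainment could differ as well as risk.
2. One 0/1 term has no parameter for notification against no notification. The model therefore cannot answer Objective 1 or supply the three pairwise comparisons in the Trial design section. If notification works at all, the reference rate is a blend whose value depends on how many patients of each kind happen to be collected.
3. An enrolled patient of a coordination team whose encounter fell outside monitoring would, under the Discussion's definition, be eligible for usual care and coded 0. That sits badly with the intention-to-treat statement in Statistical methods.

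A positive primary result could not be attributed to the randomised care transitions support alone.

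**Working it through.** **Inputs from the protocol article.** Sample size section: rates 40%, 40% and 26%; 7 patients per PACT; intraclass correlation (ICC) 0.05; 155 v 311; 80% power; two-sided 5%; 300 enrolled per site; 25–30% with events; 10–15% attrition. Allocation section: 25 + 41 = 66 PACTs.

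**1. The plan's own figure.** Design effect = 1 + (7 − 1) × 0.05 = 1.30. With unpooled variance and 1:2 allocation, n₁ = (1.960 + 0.842)² × [0.26 × 0.74 + 0.40 × 0.60 / 2] / 0.14² = 125.1. Times 1.30 this is 162.6, or 487.9 in total; with pooled variance the total is 523. The stated 466 is reproduced at ICC 0.04: 125.1 × 1.24 = 155.1, total 465.4. Power at 155 v 311 with ICC 0.05 is 75% (pooled) to 78% (unpooled). This is a side point. What matters here is that 466 is built on the 155 v 311 pooling.

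**2. Share of the comparator that is not randomised.** Events among enrolled patients: 600 × 0.25 = 150 to 600 × 0.30 = 180. Split equally, that is 75–90 per randomised arm. Filling 311 comparators then needs 311 − 90 = 221 to 311 − 75 = 236 usual-care patients: 221/311 = 71% to 236/311 = 76%.

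**3. Effect of selection (assumed rates).** Suppose both randomised arms have 40% and usual care has 50% for reasons unrelated to treatment. Bias = n₃/(n₂ + n₃) × 10 points. The rejection probability is a normal approximation, unadjusted, at design effect 1.3.

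| n (coordination / notification-only / usual care) | Bias | Standard error | Two-sided rejection |
|---|---|---|---|
| 155/155/156 | 156/311 × 10 = 5.0 points | 5.5 points | about 15% |
| 75/75/236 | 236/311 × 10 = 7.6 points | 7.2 points | about 18% |

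With usual care at 30% the bias has the same size in the other direction.

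**4. Effect of blending (assumed rates).** Suppose there is no selection and the true rates are 26%, 34% and 40%. At 155/155/156 the pooled reference is (155 × 34 + 156 × 40)/311 = 37.0%, so the model targets 11.0 points. The increment over notification is 34 − 26 = 8.0, and the difference from usual care is 40 − 26 = 14.0. The coefficient estimates neither.

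**5. Objective 1.** The planning rates are equal (40% and 40%), so the sample size assumes no notification effect. For an assumed 34% v 40%, power is about 12–16% across the splits of the 311 considered above.

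**6. Power of the randomised contrast alone, 26% v 40%.** Ranges span pooled and unpooled variance.

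| Per arm | Design effect 1.3 | Implied cluster size over 66 PACTs |
|---|---|---|
| 155 | 63–64% | 67–68% (310/66 = 4.7 per PACT, design effect 1.18) |
| 75 | 36–37% | 42–43% (150/66 = 2.3 per PACT, design effect 1.06) |
| 90 | 42–43% | 48–49% (180/66 = 2.7 per PACT, design effect 1.09) |

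These are before attrition. At 15% attrition and design effect 1.3, the 75–90 row range falls to about 31–37%.

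**The case against.** Several points on the other side stand.

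- **The Discussion is candid.** It claims randomisation only for arms 1 and 2, says that arm 3 is retrospective, and refers to quasi-experimental approaches. A reader might infer that the model makes that claim false. It does not: those arms are randomised. The narrower criticism is that the stated primary model does not use the randomised comparison the Discussion says is kept.
- **Pairwise comparisons are planned.** A reader might infer that Objective 1 has no estimate at all. The Trial design section promises each intervention against control, and the full analysis plan, not shown, may model this. What holds is that the stated primary coefficient cannot deliver it, and that no model or sample size in the article separates the two groups.
- **Part of the contrast is randomised.** To call the primary contrast simply non-randomised would go too far; all of code 1 and some of code 0 are randomised.
- **Mitigation is stated.** Controls are concurrent, and adjustment may include age, non-VHA hospital, chronic illness count, discharge diagnosis and length of stay. This may reduce selection bias, so the bias figures above describe only the unadjusted model. It does not restore randomisation.
- **The magnitudes are assumed.** The 10-point gap has no source in the article. A 50% v 40% gap would also fit a real notification effect, so the illustration isolates selection only by assumption. A flat design effect of 1.3 stands in for the random-effect model and would not describe usual-care patients who share PACTs with the coordination arm. The 75/75/236 split is derived, totals 386 rather than 466, and could change: the Discussion says enrolment or duration would be extended if encounters fall short.
- **Power is a genuine reason for the design.** The Discussion gives it as such, so separating the groups has a real price.

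The pooling cannot be dismissed as a loose example in the model text, because the sample size is built on the same pooling.

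**Conclusion.** The point holds, and it is structural: it does not depend on the illustrative rates. As written, the primary coefficient is no longer a purely randomised contrast, and it cannot separate notification from usual care. It therefore answers neither Objective 1 nor the comparison between the two randomised arms. If the stated enrolment and event rates hold and events split equally, roughly three quarters of the comparator group would be non-randomised.

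How much bias results is unknown. A 10-point selection gap would give 5.0 to 7.6 points of unadjusted bias; no gap would give none. The article's 80% power belongs to the pooled contrast and does not carry over to the randomised comparison or to notification against usual care.

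**What to change.** 1. Replace the 0/1 code with a three-level group factor: notification-only, notification-plus-coordination, usual care.
2. Report notification-plus-coordination v notification-only, in randomised patients analysed by their team's assignment, as the contrast on which causal claims about coordination rest.
3. Report each contrast with usual care separately, covariate-adjusted and labelled non-randomised. This is how Objective 1 gets its estimate.
4. If the pooled contrast is kept, label it partly non-randomised and supportive.
5. Restate the 80% power in the Sample size section, and the Discussion's claim of sufficient power for both questions, contrast by contrast.

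**Cost.** Steps 1 to 4 need a change of model wording and a protocol clarification before analysis, and no new data. The price is power for the randomised contrast at 40% v 26%, as tabulated in step 6 of the working. Reaching 80% at design effect 1.3 would take about 226–229 per arm (unpooled: 173.2 × 1.3 = 225.1, rounded up; pooled: 229), well above the 75–90 that stated enrolment yields. The sponsor would have to accept and disclose that shortfall, or use the extension of enrolment or duration that the Discussion already foresees.

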### Ethics

This protocol, along with all informed consent documents, questionnaires and data collection templates, will be reviewed and approved by the Institutional Review Board (IRB) of Indiana University as well as the VA Research & Development Committee at both the Indianapolis VA Medical Center and the Bronx VA Medical Center.

Subsequent to initial review and approval, the responsible IRBs and VHA research committees will review the protocol at least annually. The investigators will make safety and progress reports to the IRBs at least annually and within 6 months of study termination or completion. These reports will include the total number of participants enrolled, serious adverse events, reportable events (e.g., death of a patient unrelated to the study), and summaries of each DSMB [Data Safety and Monitoring Board] review of safety and/or efficacy.

Any modifications to the protocol which may impact on the conduct of the study, potential benefit of the patient or may affect patient safety, including changes of study objectives, study design, patient population, sample sizes, study procedures, or significant administrative aspects will require a formal amendment to the protocol. Such amendment will be agreed upon by the VHA Health Services and Research Department (HSR&D, the funder) and approved by the IRBs and VHA research committees prior to implementation in accordance with VHA regulations.

### Dissemination

Primary and secondary outcomes will be analyzed and published via peer-reviewed publications. Specific publications will be determined and written by the investigators as preliminary as well as final data become available for analysis. Once accepted, publications will be reported to the VHA HSR&D Service and made available publicly via PubMed Central per VHA regulations.

In addition to peer-reviewed manuscripts, the study team further intends to present preliminary and initial analyses at scientific conferences such as meetings organized by the American Medical Informatics Association, the American Geriatrics Society, and the Agency for Health Research and Quality. Furthermore, the study team will distribute findings as well as lessons learned to VHA operations teams to enable adoption and implementation of high quality care transitions throughout the VHA system. Intended stakeholders include the VHA Office of Patient Care Services- Geriatrics and Extended Care Services, Case Management and Social Work, Office of Connected Care, and the VHA Office of Health Information.

## Discussion

Our study is innovative in its use of a trial design to examine the impact of event notifications, enabled by HIE, on health outcomes. HIE has been associated with a number of benefits [36], including a reduction in expensive imaging studies [37], improved population level immunization rates [38] and completeness of disease reporting to public health authorities [39]. Given the ability of HIE to facilitate access to patient information, especially after a handoff or transfer of care, there exists a strong theoretical case for HIE to impact care coordination activities [40], such as reintegration into primary care following an acute care episode. However, recent systematic reviews of HIE [36, 41] do not include such studies. This may be due to the fact that the only prior study examining event notification [8] utilized a cohort design found to be insufficient for inclusion in a systematic review. Our study is designed to generate high quality evidence on event notification, evidence needed for assessing the impact of HIE services on patient and population outcomes in future reviews.

Our study is further innovative in its combination of arms that enable examination of a care transitions intervention pioneered by Coleman et al. [16] beyond event notification enabled by HIE. Prior studies in multiple countries have examined interventions designed to improve care transitions for older adults [42–46], yet most focus on steps that can be taken by clinical staff within emergency department or hospitals prior to discharge. Few interventions can be implemented to initiate care transitions following discharge, because there are many breakdowns in communication with external primary care providers once the patient leaves a facility. The growth in HIE networks provides an opportunity to identify a discharge event and initiate timely follow up by primary care providers. This study is designed for sufficient power to examine not only the benefit of event notification but also the additional benefit of a care transitions intervention that can activate patients to better self-manage their complex disease and medication regimens at home.

Although this study is conducted within the VHA system, the findings should be applicable to other health systems within the U.S. as well as global health systems. There is nothing inherent in the study design that precludes implementation in other settings. With respect to the informatics systems, ADT systems are widespread in health care systems as they drive many EHR and decision support system functions. Furthermore, patients cross “system” boundaries in every country, including care seeking at public and private hospitals as well as “in-network” and “out-of-network” facilities. Prior studies examining global health systems find a common pattern of poor care coordination [5]. Furthermore, a more recent analysis by Penm et al. [47] found that poor primary care coordination was more likely to occur among patients younger than 65 years. Therefore findings from this study may be applicable to care coordination for age groups beyond older adults.

The study does possess several challenges of note. First, maintaining adequate statistical power will require that a sufficient number of patients experience acute care events outside the VHA. This is not desired, but necessary to observe natural care coordination processes in addition to those influenced by the event notifications. If there are fewer than expected non-VHA encounters, enrollment will need to be increased or the study timeframe will need to be lengthened. This is one reason why we added a second phase to incorporate individuals who are unable to be approached and recruited formally into the study. Such a design is atypical for trials. However, it is impossible to predict a priori which patients will have an acute encounter outside of the integrated VHA health system.

Furthermore, although we considered using a third, “usual care” arm for enrolled patients like most trials instead of the second phase, we ultimately deemed it potentially unethical to deny patients a potentially valuable event notification intervention. Ethical dilemmas with respect to randomization are common in biomedical informatics intervention studies [48], which often require quasi-experimental approaches [49]. Moreover, the number of primary care medical homes distributed across the two sites would limit statistical power if they were divided into thirds for randomization. Therefore we opted to retrospectively use patients who did not enroll in the study or who enrolled but had a non-system encounter outside the prospective monitoring period as a control arm. Doing so enables us to retain the robustness of randomization in arms 1 and 2 while maintaining statistical power with arm 3.

Another challenge for the study will be the implications of the findings. Should the care transitions intervention in combination with event notification prove to be superior, how can the VHA feasibly disseminate this approach? Furthermore, how can health systems economically sustain such an approach? The care transitions intervention requires active monitoring by a social worker or other care coordinator following discharge from the “out-of-network” facility. A home visit and phone monitoring may not be possible in every care transition. A challenge for our team will be to determine under what circumstances a superior but more intense intervention would be cost effective for the VHA or another health system.

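### The Discussion claims sufficient power for notification and for the added benefit of care transitions, but the only sample-size calculation covers coordination against the other two groups combined

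*Protocol article*

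**What the plan says.** Under Trial design, three comparisons are planned: "Comparisons will be performed between each intervention group and the control group as well as between the two intervention groups". Only arm 2 (notification plus coordination) against arm 1 (notification only) is randomised. Allocation assigns PACTs to these two arms "using lists of computer-generated random numbers in a 1:1 ratio", and usual care is identified retrospectively.

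Under Sample size, both comparator groups are given one common rate: "the notification-only group as well as the usual care group will have a 40% readmission rate". For arm 2 the assumption reads: "the notification-plus-coordination group will have a 26% readmission rate in the 90-day post-discharge period". The requirement is then "we need to observe a total of 466 patients with non-VHA hospitalizations or ED visits". Its breakdown is given as "155 in the notification-plus-coordination group and 311 combined in the notification-only and usual care groups". The target for this number is "to detect an effect size of 0.35 with 80% power and a two-tailed test at 5% significance". The intraclass correlation is 0.05 with an average of 7 subjects per PACT. Statistical methods gives the same grouping as its example coding of the primary model: coordination against notification only or no notification.

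The Discussion then claims sufficient power on two counts. One is whether notification itself helps; the other is worded: "but also the additional benefit of a care transitions intervention that can activate patients to better self-manage their complex disease and medication regimens at home". The same paragraph describes this as examining care transitions beyond notification.

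**The concern.** A benefit additional to notification is the difference between arm 2 and arm 1. The 80% belongs to a different comparison, in which the comparator is about twice as large because retrospective usual-care patients are added. Adding them estimates the increment over notification only if notification alone has no effect, and that is what Objective 1 sets out to examine.

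The first half of the Discussion sentence has a further difficulty. The sample-size assumptions put notification-only and usual care at the same rate, so they contain no notification effect to detect.

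The consequence is for interpretation. A reader who trusts the sentence would take a non-significant arm 2 v arm 1 result, or a non-significant notification result, as evidence of no benefit from an adequately powered study.

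**Working it through.** **Inputs.** From Sample size: 26% and 40%; two-sided 5%; 155 v 311; ICC 0.05; 7 per PACT; 300 enrolled at each of two sites; 25-30% with an event; 10-15% attrition. From Allocation: 25 + 41 = 66 PACTs, randomised 1:1, so about 33 per arm. Assumption: the 311 splits about equally between arms 1 and 3. The article gives no split; 1:1 randomisation makes similar active arms the natural reading.

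**Formulas.** Design effect DE = 1 + (m - 1) x ICC = 1 + 6 x 0.05 = 1.30. Unpooled normal approximation: SE = sqrt(DE x [0.26 x 0.74/n2 + 0.40 x 0.60/nC]), where n2 is arm 2 and nC the comparator. Power = Phi(0.14/SE - 1.96).

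**1. The article's own figure (155 v 311).** SE = sqrt(1.30 x [0.1924/155 + 0.2400/311]) = 0.0512; 0.14/0.0512 = 2.74; power = 78.1%. This is within two points of the stated 80%. A pooled variance gives 75.3%. At ICC 0.04 (DE 1.24) the unpooled value is 80.0%.

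**2. Arm 2 v arm 1 at about 155 per arm.** SE = sqrt(1.30 x [0.1924/155 + 0.2400/155.5]) = 0.0602; 0.14/0.0602 = 2.33; power = 64.3% (pooled variance 63.5%).

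The figure of 7 per PACT looks like 466/66 = 7.06, an average over all three groups. Within two arms of 155 it is about 155/33 = 4.7, so DE = 1 + 3.7 x 0.05 = 1.185.

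| Variant, about 155 v 155 | Power (unpooled) |
|---|---|
| DE 1.30 (stated inputs) | 64.3% |
| DE 1.24 (ICC 0.04) | 66.4% |
| DE 1.185 (4.7 per PACT) | 68.3% |
| DE 1.00 (no clustering) | 75.6% |

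A continuity correction at DE 1.30 lowers the figure to about 58%.

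**3. Dependence on the split (155 in arm 2, DE 1.30).**

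| Arm 1 patients | Pooled variance | Unpooled |
|---|---|---|
| 100 | 54% | 53% |
| 200 | 68% | 70% |
| 233 | 71% | 73% |
| all 311 | 75% | 78% |

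No split reaches 80% at the stated design effect.

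**4. What the enrolment forecast delivers.** 600 x 0.25 = 150 and 600 x 0.30 = 180 index patients over both randomised arms, or 75-90 per arm.
- At DE 1.30, power is 36-42% (pooled variance) or 37-43% (unpooled).
- With 75/33 = 2.3 to 90/33 = 2.7 per PACT, DE is about 1.06-1.09 and unpooled power is 43-49%.
- If the 10-15% attrition falls on these patients, 150 x 0.85/2 = 64 to 180 x 0.90/2 = 81 per arm remain. Power at DE 1.30 is then about 31-38% (pooled variance).

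**5. Detectable difference.** At about 155 per arm and 80% power, the detectable rate against 40% is 23.4% (DE 1.30) to 24.1% (DE 1.185), a relative reduction of about 40-41% rather than 35%. For 26% v 40%, 80% power needs (1.96 + 0.84)^2 x (0.1924 + 0.2400)/0.14^2 x 1.30 = about 225 per arm (229 with pooled variance).

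**6. Notification v usual care.** The assumed rates are 40% and 40%. The difference is zero, so the rejection probability equals the 5% significance level and no power can be stated.

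**The case against.** The operative design is consistent: Sample size and the example model coding use the same combined comparison. The pairwise comparisons are not called primary, and secondary contrasts need not reach 80%. The Discussion sentence gives no number, and a full protocol or SAP that is not shown may hold pairwise calculations. All of this is fair. It means the primary analysis needs no change. It does not rescue an affirmative statement that the article's own figures do not support.

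Three stronger readings are tempting and should be resisted:

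- A reader might infer that the 80% is itself a material error, or that 466 can be traced to one particular formula. The 78.1% is close enough to count as reproduction, if slightly below the stated value. The source of 466 cannot be established: at the stated inputs a 1:2 formula gives about 488-523 in total, and a 1:1 formula gives about 458.
- A reader might take 64-68% as the power the trial will have. It holds only if about 155 index patients per randomised arm are observed, and the printed enrolment forecast implies about half that.
- Conversely, a reader might treat 36-49% as settled. The Discussion allows enrolment to be increased or the timeframe lengthened, so 155 per arm is not excluded.

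The statement that no split reaches 80% also has a limit. At DE 1.24, placing all 311 in notification-only gives 80.0%, but that leaves no usual-care group.

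**Conclusion.** The claim is wrong as written, in both halves. The stated power supports one comparison only, arm 2 against arms 1 and 3 combined. Even if the target of 466 is met and the assumed effect is true, the randomised comparison would miss that effect about one time in three. At the forecast event yield it would miss it more often than not. No power for a notification benefit follows from the stated assumptions.

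The size rests on 26% v 40%, ICC 0.05, a normal approximation and, for the 155-per-arm figures, an equal split of the 311. The conclusion that arm 2 v arm 1 falls short of 80% does not depend on the split at the stated design effect. This is an unsupported power statement, not a fault in the primary model.

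**What to change.** Keep the sample size and the primary analysis unchanged, and amend two places.

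1. **Sample size.** State that the 80% (about 78% by the unpooled normal approximation at ICC 0.05 and 7 per PACT) applies only to arm 2 against arms 1 and 3 combined. Give the arm 2 v arm 1 power for 26% v 40% as conditional on index patients per arm: about 64-68% at 155 per arm, where the drop detectable with 80% power is from 40% to about 23-24%; and about 36-49% at the 75-90 per arm implied by the enrolment forecast, lower after attrition. State the assumed split of the 311.
2. **Discussion.** Remove both halves of the sufficient-power sentence, or restrict it to the combined comparison. Removing only the care-transitions half would leave the notification claim standing with no support. Add that a non-significant pairwise result will not be read as evidence of no benefit.

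The cost is wording, with no extra patients. The downside is that the stated power for the pairwise comparisons becomes less favourable.
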